## Discussion

The ability of a therapy to diminish inflammation, such as peripheral and axial enthesitis, and to prevent or halt structural progression is fundamental in treating patients with axSpA and PsA. To clarify these therapeutic effects is of utmost importance, as they are essential for preventing pain and functional impairment in the patients.

In PsA, pain caused by enthesitis can be challenging to distinguish from pain resulting from central sensitization, and overlapping fibromyalgia is common in PsA, as well as in axSpA [56, 57].

Since diagnosing enthesitis through clinical methods is difficult and uncertain, clinically based outcome measures for enthesitis may not yield reliable results. WB-MRI offers the capability to objectively assess joints and entheses throughout the entire body. The DAPHNE study aims to utilize this comprehensive imaging method, along with the validated MRI WIPE scoring system, to investigate the unexplored effects of ixekizumab on enthesitis and peripheral joint inflammation.

In addition to the evaluation of inflammation in peripheral joints and entheses, axial inflammation and structural lesions will be evaluated using the CanDen MRI definitions. These definitions have recently been adopted by ASAS [58]. Inflammation in relation to each discovertebral junction, in synovial joints such as facet joints, in costo-vertebral and costo-tranversal joints and in posterior entheses at the spinous process and transverse processes can be separately assessed by this method, as can the development of structural lesions such as fat metaplasia, bone erosion and new bone formation at the individual locations. To our knowledge, no such data in ixekizumab treated patients exist.

However, radiography using the mSASSS method for structural damage assessment in the spine is still yet the only validated and recommended method for this purpose [59]. Nevertheless, low-dose CT has been shown to outperform radiography in evaluating structural damage in the spine [60–62] and although low-dose CT involves significantly less radiation than conventional CT, it still exposes patients to ionizing radiation. In contrast, synthetic CT is based on an MRI sequence, meaning that patients are not exposed to radiation. Beyond the significant advantage of eliminating radiation exposure, the MRI examination could then offer both the excellent ability to visualize inflammation of conventional MRI and the better visualization of structural damage provided by sCT.

Currently, there are no published studies on the ability of this relatively new sCT method to detect and monitor structural changes in the spine of patients with axSpA and PsA. As it is known that in radiographic axSpA, most progression in structural changes is seen in the spine [22], the ability of an imaging method to reliably detect and monitor structural changes in the spine is crucial to its use, especially in clinical trials.

Since no data exist on the objective assessment of enthesitis, inflammation of the posterolateral spinal segments, or structural progression in the spine using modern imaging during ixekizumab treatment neither in PsA nor axSpA, a longitudinal study hereof would provide important new evidence on the effectiveness of ixekizumab across these different disease domains.

In the DAPHNE study repeated MRI (including MRI-based synthetic CT) and low-dose CT scans will be performed, and the patterns of structural damage will be explored with the purpose of improving axial structural damage assessments in patients with axSpA and PsA. The study will compare the different imaging modalities and images will be evaluated with the currently available methods for structural damage assessment in the spine and the sensitivity to change will be tested. In addition, further exploration and optimization/development of new assessment methods will be done. The latter will first be possible after reading the images, as this will then reveal the limitations of the current methods and highlight areas where improvements are needed. Afterward, when the new methods are developed, it is the plan to refine and validate these, and thereafter to take the methodologies to international endorsement.

A non-randomized trial study design was chosen for several reasons: Firstly, the primary and 6 out of 7 secondary objectives are based on imaging (MR, CT, and radiography). All images will be assessed blinded to diagnosis, chronology, and clinical and other imaging findings according to internationally recognized scoring systems. Thus, observed changes will not be subject to bias and a control group is not required. Secondly, the advantages of not having a placebo-controlled trial include that the patients are not exposed to a period without active therapy. This fact minimizes patient discomfort and increases the willingness of patients to participate in the study.

In conclusion, the DAPHNE study is anticipated to significantly improve our understanding of the diverse disease manifestations in patients with axSpA and PsA, and how they respond to ixekizumab treatment. Additionally, the study will provide valuable insights into new and improved imaging examination and evaluation methods.

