In this study, we aim to address the abovementioned gaps by conducting a longitudinal investigation of the effects of ixekizumab on peripheral and axial inflammation and structural damage in patients with axSpA and PsA. Through comprehensive assessment using advanced imaging techniques such as WB-MRI and detailed MRI evaluation of the spine, including sCT, and low-dose CT, we seek to provide valuable information on the therapeutic effectiveness of ixekizumab across different disease domains. The primary objective is to assess the effect of ixekizumab on the total inflammatory burden in the entire body (peripheral and axial joints and entheses) of patients with axSpA and PsA, as assessed by WB-MRI.

Here we report the design of the DAPHNE study.

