### Participants

Participants will be recruited from rheumatological outpatient clinics in the capital region of Copenhagen. Participants in this study are all patients followed by the participating rheumatologic departments. The participant must have moderate to high disease activity, and it must have been decided by the individual departments (at a conference between rheumatologists), that the patient should start or switch biologic treatment.

The patient is invited to participate in the study by a physician in the rheumatological outpatient clinic during a routine visit. Oral and written information will be provided. If the patient agrees to participate, an informed consent form is signed. A screening visit is performed to ensure that the patient meets the criteria for participation.

Inclusion criteria for both groups (axSpA and PsA) are age $$ \ge $$ 18 years at the time of consent, a clinical indication for a biological drug as assessed by the treating physician, sufficient contraception for women in addition to the ability and willingness to provide written informed consent and compliance with the requirements of the study protocol.

For patients with axSpA additional inclusion criteria are a diagnosis of axSpA according to the Assessment of SpondyloArthritis International Society (ASAS) classification criteria [27, 28], active inflammation on MRI of the SIJs and/or spine [29] as evaluated by a central SpA imaging expert and/or radiographic modified New York criteria [30] fulfilled, and total back pain as measured on a VAS scale ≥40 mm (0–100 mm) at baseline.

For patients with PsA additional inclusion criteria are PsA according to Classification Criteria for Psoriatic Arthritis (CASPAR) [31], negative rheumatoid factor (RF) and anti-cyclic citrullinated peptide (anti-CCP), and ≥ 1 tender and swollen joint in addition to two further anatomical localizations with clinical signs of inflammation (i.e., tender enthesis and/or tender and/or swollen joint) assessed at screening and baseline. For patients to fulfill the axial PsA component they must have imaging documented axial involvement on MRI, radiography, or low-dose CT as judged by a central SpA imaging expert.

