#### Image evaluation

Image evaluation will be by state-of-the-art internationally validated methods for radiographs (modified New York criteria [30] and the mSASSS [33] method), MRI (SPARCC sacroiliac inflammation [17] and structural (SSS) [34] scores, Canada-Denmark spine score of inflammation and damage [19, 20]), and OMERACT Whole-body MRI scores of peripheral enthesitis and joint inflammation scores (WIPE) [13, 14]. Images will be evaluated by readers blinded for diagnosis and clinical and other imaging findings. Furthermore, new lesion definitions and evaluation methods for synthetic CT and low-dose CT will be sought developed and explored.

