### Statistics

#### Sample size calculation

The primary hypothesis of this study is that ixekizumab will reduce the total inflammatory burden in the entire body of patients with axSpA and PsA, as assessed by WB-MRI. All patients in this study will be treated with ixekizumab and the primary endpoint relates to identifying changes within groups. A guiding sample size calculation was done.

A previous investigator-initiated study with 53 axSpA patients treated with a bDMARD (golimumab) using WB-MRI as an outcome measure showed that the mean change in MRI-total inflammation (MRI axial inflammation + MRI peripheral inflammation (joints and entheses)) at week 52 was 24.8 (*p* < 0.001) with a standard error of 3.6 [55].

The change in WB-MRI total inflammation is the primary endpoint in the current study. If the expected mean of the paired differences is 24.8 and the expected standard deviation is 26.2 (corresponding to a standard error of 3.6) the study would require a sample size of 12 (numbers of pairs) to achieve a power of 0.80 and a level of significance of 0.05 (two-sided).

With an expected drop-out rate of 20% at month 12 the required sample size would be 14 patients.

It is planned to include 65 patients (≥25 with each diagnosis).

Sub-group analyses in regard to the primary endpoints for all groups (axSpA vs. PsA, WB-MRI remission vs. WB-MRI non-remission and clinical responders vs. clinical non-responders) are planned. For this matter, the calculated sample size is considered appropriate to detect a statistically significant change in the total inflammatory burden in the entire body as assessed by WB-MRI at month 12 in both the overall study population and in the individual sub-groups during treatment with ixekizumab.

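### Blinded image reading limits reader bias only; it does not make the change from baseline free of bias, so a significant fall cannot by itself show an effect of ixekizumab

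*Protocol article*

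**What the plan says.** The study is a two-year, open-label, single-arm trial. Under Sample size calculation the article states: "All patients in this study will be treated with ixekizumab and the primary endpoint relates to identifying changes within groups". The Discussion gives two reasons for not randomizing. The first is blinded reading: "All images will be assessed blinded to diagnosis, chronology, and clinical and other imaging findings according to internationally recognized scoring systems". From this it concludes: "Thus, observed changes will not be subject to bias and a control group is not required". The second is that patients are spared a period without active treatment.

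The aims are worded causally. In the Introduction: "The primary objective is to assess the effect of ixekizumab on the total inflammatory burden in the entire body". Under Sample size calculation: "The primary hypothesis of this study is that ixekizumab will reduce the total inflammatory burden in the entire body". Statistical analysis tests within-group change with a paired t-test or Wilcoxon signed rank test, in an intention-to-treat population of all included patients.

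Blinding is also described in the Abstract (Methods) and under Image evaluation: "Images will be evaluated by readers blinded for diagnosis and clinical and other imaging findings". Neither place lists chronology.

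**The concern.** A reader who does not know the order of the scans cannot score later scans lower out of expectation. That is all this safeguard provides. It gives no information on what the scores would have done without ixekizumab. The article itself describes several routes by which the month-12 score could change for other reasons, and reader blinding touches none of them.

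If the sentence stands, it licenses the step from a significant fall to a drug effect. The paired test cannot support that step, because its null hypothesis is zero change and not the change expected without the drug. With far more patients than the sample size calculation requires, a modest fall is enough to reject that null.

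**Working it through.** **Sources of non-drug change that the article describes**

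- *Entry at high activity (Participants).* All patients need moderate to high disease activity. AxSpA patients need back pain of at least 40 mm, and one of their two imaging entry routes is "active inflammation on MRI of the SIJs and/or spine". PsA patients need a tender and swollen joint plus two further inflamed sites. Some regression to the mean is to be expected.
- *Co-treatment (Study interventions).* Doses of csDMARDs and NSAIDs must be fixed only up to month 4. Glucocorticoid injections into peripheral joints and entheses, which are scored sites, are allowed from month 4 to month 11.
- *Treatment changes (Assessments; Statistical analysis).* Patients above the ASDAS or DAPSA threshold at month 4 change treatment, stay in follow-up and remain in the intention-to-treat set. Their month-12 change may partly reflect another drug.
- *Drop-out (Sample size calculation).* 20% is expected by month 12.
- *Natural course.* No untreated group shows it.

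**The plan's own sample size**

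Inputs: mean change 24.8, standard error 3.6, 53 patients, power 0.80, two-sided level 0.05.

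- SD = 3.6 × √53 = 26.2, as stated.
- Paired t-test power from the noncentral t distribution: 80.7% with 11 pairs and 84.7% with 12. The stated 12 is adequate; the minimum is 11.
- Allowing for drop-out: 11/0.8 = 13.75, rounded up to 14; 12/0.8 = 15. The stated 14 is close enough.

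The calculation is sound for the question whether the mean change is zero.

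**Smallest mean fall that is significant**

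Formula: t(0.975, n−1) × 26.2/√n.

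| Patients with month-12 data | Standard error | Smallest significant fall | Share of 24.8 |
|---|---|---|---|
| 65 × 0.8 = 52 | 3.63 | 7.29 | 29% |
| 65 | 3.25 | 6.49 | 26% |

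These thresholds use only the article's SD, planned number and drop-out rate.

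**What this means if the drug did nothing**

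The documents give no untreated change, so the first column is an assumption over a range and not an estimate. It keeps the SD at 26.2.

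| Assumed non-drug fall | Chance of significance, n = 52 | Chance of significance, n = 65 |
|---|---|---|
| 10% of 24.8 (2.48) | 10% | 12% |
| 20% (4.96) | 27% | 32% |
| 30% (7.44) | 52% | 62% |
| 40% (9.92) | 76% | 85% |
| 50% (12.4) | 92% | 96% |

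The table shows only that the test reacts to any change. It does not say which row applies.

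**The case against.** The strongest defence is that this is rationale in a Discussion and that most of the operative text is already modest. The endpoint is a change from baseline in treated patients, the sample size section speaks of changes within groups, and the design is openly labelled open-label. Correcting the sentence alters no endpoint, test or sample size. All of that stands, and it limits the severity. It does not rescue the sentence, which asserts a property the design lacks, nor the causal objective and hypothesis.

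Co-treatment is also partly controlled. csDMARD and NSAID doses are fixed to month 4, glucocorticoid injections are barred from month 11 until the month-12 assessments are done, and other potentially disease-modifying drugs are prohibited. The gap after month 4 remains.

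Some stronger readings are tempting but not supported:

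- *That a control arm is required.* Avoiding a period without active therapy is a legitimate reason for having no placebo arm. The fault lies in the first reason and in the causal wording.
- *That regression to the mean can be sized.* This would need selection on the whole-body score itself, its between-patient SD and its test-retest correlation. The article gives none of these. Entry is mainly clinical, the MRI criterion is one of two axSpA routes, and PsA entry requires no MRI inflammation. Selection on a clinical variable only weakly related to the MRI score would produce less regression.
- *That one scan serves both for selection and as baseline.* Table 2 puts the only pre-treatment whole-body MRI at screening, but Participants does not say which MRI establishes eligibility.
- *That the blinding statements contradict each other.* The shorter lists omit chronology; they do not deny it.
- *That the structural endpoints share the fault.* Key secondary endpoints 4 and 5 are descriptive and do not test a drug effect.
- *That the golimumab result could serve as a benchmark.* It is itself a within-group change, in axSpA patients only, so it cannot separate drug effect from other change.

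**Conclusion.** The point holds for the inference and the causal wording; it should be fixed. Blinded reading limits reader bias and leaves the other sources of change uncontrolled. A mean fall of about 7.3 units with 52 completers, or 6.5 with 65, is significant whatever produced it. This assumes the paired t-test, the article's SD of 26.2 and, for 52, its 20% drop-out. The size of any non-drug change is unknown from the documents.

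The fall itself can be estimated, and a very large fall may be suggestive. What the design cannot do is attribute the fall to ixekizumab on the strength of a p-value against zero. Because non-responders may change treatment from month 4 and stay in the primary analysis, the month-12 result describes a strategy that starts with ixekizumab, not ixekizumab given throughout.

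**What to change.** 1. In the Discussion, delete the sentence on bias and the control group, or limit it to saying that blinded reading reduces reader bias. Keep the second reason for the single-arm design.
2. State the absence of a control group as a limitation, naming regression to the mean, natural course, co-treatment, treatment changes after month 4 and drop-out.
3. Word the primary objective, hypothesis and conclusion as change from baseline to month 12 during a treatment strategy starting with ixekizumab, reported as an estimate with a 95% CI.
4. Add chronology to the blinding statements in the Abstract and under Image evaluation, so that they match the Discussion.

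The cost is a more modest claim. No new arm, scan, endpoint or sample size is needed.

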## Data Availability

No datasets were generated or analysed during the current study.
